# Whole School SEND (WSS) Review: study protocol for a two-arm pragmatic parallel cluster randomised controlled trial in 160 English secondary schools

**DOI:** 10.1186/s13063-021-05280-y

**Published:** 2021-05-10

**Keywords:** Cluster randomised, Special educational needs, Attainment, Wellbeing, Schools

## Abstract

**Background:**

The trial will study the effects of the Whole School SEND Review on secondary school pupils in English mainstream education, to understand the impact of the intervention on academic attainment, wellbeing, and school attendance. The Review is designed to facilitate whole-school change through providing enhanced, intensive and sustained support and training in inclusive education for school special educational needs coordinators and leadership teams. The trial will have a specific focus on pupils designated as having special educational needs or disabilities.

**Methods:**

We recruited 160 English secondary schools (approx. 58,000 pupils across two cohorts) to a two-arm pragmatic parallel cluster randomised controlled trial, with allocation at the school level. Randomisation will be stratified by school region. The primary outcome is attainment in English language (using standardised national test results at 16 years) for pupils designated as having a special educational need (approx. 4000 pupils). Secondary outcomes will be measured for pupils both with and without a special educational need designation and include pupil wellbeing (measured using the Strengths and Difficulties Questionnaire), absences and exclusions, and attainment in Mathematics and English language at 16 years. The intervention will be implemented from July 2021 and analysis of outcomes (for the year 9 cohort) will take place in September 2023, with further analysis (for the year 8 cohort) in September 2024 if the evaluation shows that acceptable implementation fidelity has been achieved.

**Discussion:**

Pupils with special educational needs represent a significant and often vulnerable part of the secondary school population, are disproportionately likely to be excluded from school, eligible for free school meals, or supported by children’s social care. Despite these multiple important areas of need, school leaders report substantial challenges in making additional provision for this group. Previous research has highlighted the development of inclusive school cultures (rather focusing primarily on targeted individualised approaches) as being important. This trial will investigate how an intervention designed to drive whole school change may lead to outcomes for pupils with and without a special educational needs designation. As such, this trial is expected to make an important contribution to research evidence and to UK educational policy.

**Trial registration:**

ISRCTN registry ISRCTN11339306. Registered on 12 March 2020 (retrospectively registered).

## Introduction

### Background and rationale {6a}

The trial will study the effects of the Whole School Send (WSS) Review on secondary school pupils in English mainstream education to answer research questions relating to academic attainment, school attendance, and wellbeing. The intervention has been developed by the National Association for Special Educational Needs (nasen), and the evaluation is being sponsored and funded by the Education Endowment Foundation (EEF). Manchester Metropolitan University have been appointed as researchers.

A group of pupils of particular interest are pupils with special educational needs or disabilities (SEND) who represent a significant and often vulnerable part of the secondary school population (14.9%) [2]. School leaders report substantial challenges in making additional provision for SEND pupils, who are disproportionately likely to be excluded from school, to be eligible for free school meals and to be ‘looked after’ or identified as a child in need [3].

Research over recent years has highlighted the importance of inclusive pedagogy for all learners [4–6], pointing to the need to develop schools as inclusive learning environments, rather than focusing primarily on specialist approaches for individuals identified with SEND. Equally, there is a strand of research in the field of inclusive education over the last thirty years addressing the development of more inclusive practices with learners with SEND, as a whole-school development issue [7]. A key example is the Index for Inclusion [8], which provides a process and resources to support inclusive school development.

The WSS Review is best understood against this backdrop of wider research examining inclusive school cultures. The WSS Review process includes the following:
SEND Co-ordinator (SENDCo) training on reviewing and peer mentoring provided by an experienced SEND reviewer.The use of an evidence-based framework which draws on a school’s current information, robust data and contextual factors to structure the review.Peer-to-peer support and a reflection network to facilitate a collaborative, localised and grassroots approach to developing SEND provision.

The process reflects the premise that excellent teaching for pupils with SEND is excellent teaching for all, but there is a dearth of rigorous evaluation evidence relating to specific whole-school level interventions that are relevant to secondary schools and can be adopted at scale.

The WSS Review was developed by nasen in response to the Department for Education (DfE) identifying a need for schools to access support for implementing 2014 Special Educational Needs and Disability (SEND) reforms [9]. DfE guidance encourages schools to commission a review using the WSS materials, to reflect on SEND provision and explore different approaches to raising attainment.

An evaluation of the initial DfE contract for WSS delivery^9^ noted evidence of promise in terms of the impact at the school level, for example:
The process enabled schools to build on what they were already doing well for pupils.More non-specialist SEND teachers were willing to look reflectively at their classroom practice.Subject leaders became more aware of SEND practice and curriculum differentiation.A wider awareness of the value of pupil progress data and its use in future curriculum planning was developed.SEND operational practices were changed in some schools.Peer-to-peer mentoring was adopted by some teachers/groups outside of SEND.The use of peer-to-peer mentoring was valued by all participants.

However, the evaluation noted that there were particular challenges with the review process in secondary school settings, due to the size of such institutions resulting in more children designated as SEND and the greater chance of inconsistencies in practices and staff attitudes to SEND provision, as well as the behaviour of SEND teams working independently of each other [9]. A further additional challenge relates to the tension between secondary schools working together and the competition between them in relation to student recruitment.

The evaluation did not specifically evaluate the effects of the WSS Review on pupil attainment, attendance and wellbeing, and this is therefore a logical next step, particularly given the anticipated impacts of the WSS Review on pupils. Furthermore, the WSS Review includes a specific focus on learners with identified SEND whereas other initiatives have tended to give greater emphasis to the need to move beyond SEND to a broader approach to include all learners. This trial will therefore investigate the outcomes for pupils with and without a SEND designation.

### Objectives {7}

The primary objective of this trial is to test the efficacy of the WSS Review at *raising attainment in English Language at General Certificate of Standard Education (GCSE)* among pupils designated SEND. Other objectives are to test the efficacy of the WSS Review (for pupils both with and without a SEND designation) at:
Raising attainment in GCSE mathematicsReducing absences and exclusions from schoolImproving pupils’ wellbeing

The trial is therefore designed to test the WSS Review theory of change (see the ‘Discussion’ section), which assumes the widespread effects of the intervention towards transformational change both for pupils with and without a SEND designation. It is expected that this to occur through fostering and promoting a more inclusive and supportive school culture and that the intervention will have a direct effect on the classroom through encouraging SENDCos to engage more fully with both teaching practice and the learning environment. We therefore also expect a consequent improvement in pupils’ attainment, particularly among pupils designated SEND. The WSS Review is hypothesised to enhance the inclusivity and supportiveness of the school, and as such is anticipated to reduce absences and exclusions particularly among pupils designated SEND. It is also expected that the Review will improve pupils’ wellbeing through similar mechanisms.

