**Secondary outcomes**				
Attainment	Mark obtained in GCSE mathematics	Exam boards via schools	Continuous	Pupils with a SEND designation
				All pupils
	Grade obtained in GCSE English language	Exam boards via schools	1–9; 0 (unclassified)	Pupils with a SEND designation
	Grade obtained in GCSE mathematics	Exam boards via schools	1–9; 0 (unclassified)	Pupils with a SEND designation
Attendance and exclusions	Unauthorised absences	Schools	Count of number of authorised absences in school year	Pupils with a SEND designation
	Authorised absences	Schools	‘1’ = unauthorised absence observed in the relevant school year, ‘0’ otherwise	Pupils with a SEND designation
	Exclusions	Schools	‘1’ = exclusion observed in the relevant school year, ‘0’ otherwise	Pupils with a SEND designation
Wellbeing	Difficulties	Pupil self-report	Total number of difficulties (max 20)	Pupils with a SEND designation
				All pupils

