#### Secondary analysis

The secondary analysis will involve estimation of effects on a range of outcomes discussed previously for the full year-group cohort samples (years 8 and 9) and for SEND pupils only (years 8 and 9).

Table 3 sets out the secondary analysis to be conducted on the full cohort samples. The analysis for years 8 and 9 will appear in separate reports. Hypothesis tests for the treatment effects in each specification will be reported in the form of *p* values and 95% confidence intervals. For the secondary analysis, treatment effect estimates based on continuous outcomes will be reported as effect sizes (Hedges’ *g*), where outcomes are binary as relative risk ratios and for count outcomes as incident rate ratios. Table 4 sets out the secondary analysis to be performed on the SEND only subsamples.

**Table 3 Tab3:** Secondary analysis—model specifications—full cohort samples years 8 and 9 cohorts (as at September 2020)

Dependent variable	Model	Intervention group indicator	Strata indicator	Covariates	Cohort (at 09/20)

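### Reducing absences and exclusions is an objective for pupils with and without SEND, but every planned analysis of these outcomes is confined to SEND pupils

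*Protocol article*

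**What the plan says.** Three places set the scope broadly.

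- Objectives {7}: "Other objectives are to test the efficacy of the WSS Review (for pupils both with and without a SEND designation) at" raising GCSE mathematics attainment, reducing absences and exclusions, and improving wellbeing.
- Abstract, Methods: "Secondary outcomes will be measured for pupils both with and without a special educational need designation". The same sentence goes on to name absences and exclusions.
- Background and rationale {6a}: "This trial will therefore investigate the outcomes for pupils with and without a SEND designation".

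The analysis sections are narrower. In Table 1 the exclusions row (coded 1 for an "exclusion observed in the relevant school year") and both absence rows name SEND pupils as the only analysis population. The Secondary analysis section defines two samples, the full year-group cohorts and SEND pupils only. It adds: "Table 4 sets out the secondary analysis to be performed on the SEND only subsamples". The negative binomial model for authorised absences and the logistic models for unauthorised absence and exclusion appear in Table 4 only. Table 3, for the full cohorts, lists the English mark, the mathematics mark and the SDQ total.

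The Objectives section also expects a larger benefit in one group: the Review "as such is anticipated to reduce absences and exclusions particularly among pupils designated SEND".

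**The concern.** The objective and the analysis populations disagree, and the article itself fixes both. If the tables are followed, one of the three secondary objectives is tested in only one of the two groups it names. A final report could then say nothing about absence or exclusion in most pupils of the participating schools, although the intervention is meant to change the whole school.

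If the team notices the gap after outcome data arrive and fills it then, the added analyses could be criticised as data-driven. Settling it beforehand avoids that.

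**Working it through.** **1. Each outcome traced through the tables.**

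| Outcome | Populations in Table 1 | Full-cohort model (Table 3) | SEND-only model |
|---|---|---|---|
| GCSE English mark | SEND; all pupils | yes | yes (primary analysis) |
| GCSE mathematics mark | SEND; all pupils | yes | yes (Table 4) |
| SDQ total difficulties | SEND; all pupils | yes | yes (Table 4) |
| GCSE English and mathematics grades | SEND | no | yes (Table 4) |
| Authorised absences | SEND | **no** | yes (Table 4) |
| Unauthorised absence | SEND | **no** | yes (Table 4) |
| Exclusion | SEND | **no** | yes (Table 4) |

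Of the three listed secondary objectives, mathematics attainment (through the mark) and wellbeing (through the SDQ) each have a full-cohort model. Absences and exclusions have none. Table 1 separates the two populations for other outcomes, so the SEND-only entries carry meaning.

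**2. Is there a data reason?** None is stated.

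- Secondary outcomes section: unauthorised absence and exclusion are defined for each pupil.
- Outcome data section: absence and exclusion data are obtained for the year 9 cohort (2022/2023) and the year 8 cohort (2023/2024), with no SEND restriction.
- Baseline data section: 2019/2020 absence and exclusion data are collected for each pupil.

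**3. Share of the cohort left out.** Inputs from Sample size {14}: 180 pupils per cohort per school, about 14% SEND, 160 schools.

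- The plan's own figure: 0.14 × 180 = 25.2, given as 25. It reproduces.
- Without SEND: 180 − 25 = 155 per school and cohort; 155/180 = 86.1%.
- Over 160 schools: 155 × 160 = 24,800 of 28,800 pupils per cohort.

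**4. Would a full-cohort estimate be enough?** It would supply the missing model, but it would not isolate the non-SEND group. On a linear scale, with equal weight per pupil, the pooled effect is about 0.139 × (SEND effect) + 0.861 × (non-SEND effect). For example, a SEND effect of 0.20 with none in other pupils pools to 0.139 × 0.20 = 0.028.

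For a crude risk ratio the weights also depend on event rates:

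pooled RR = w × RR(SEND) + (1 − w) × RR(non-SEND), with w = 0.139 r(S) / [0.139 r(S) + 0.861 r(N)],

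where r(S) and r(N) are the control-arm event rates. The Background says SEND pupils are disproportionately likely to be excluded, so r(S) > r(N) and w exceeds 0.139 for exclusion. The non-SEND estimate should therefore be reported as such.

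**5. Precision.** Table 2 concerns a continuous mark, with pre-test correlations of 0.70 (pupil) and 0.32 (school) and an intraclass correlation of 0.20. For SEND pupils, with 157 degrees of freedom (multiplier about 2.82):

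2.82 × √[0.20 × (1 − 0.32²)/(0.25 × 160) + 0.80 × (1 − 0.70²)/(0.25 × 160 × 25)] = 0.197,

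which matches the stated 0.20. These inputs do not carry over to one count and two binary outcomes. The article gives no event rates for them, so no minimum detectable effect can be computed.

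**The case against.** The strongest reply is that the SEND-only choice is deliberate. Tables 1, 3 and 4 agree with each other, and the Attendance and exclusions section motivates these outcomes partly by unmet needs of SEND pupils leading to poor attendance. On this view the analysis is right and the objective is loosely worded. This stands as far as the remedy goes: narrowing the wording would also remove the contradiction. It does not remove the contradiction as printed. The same section also appeals to a change in the culture of the whole school.

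A second reply is that an article leaves detail to the full online protocol or an analysis plan, neither of which is shown. That is fair for an additional effect-modification analysis. It does not cover the analysis population of each outcome, which the article states in three tables.

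A third reply is that the phrase about both groups can mean the pooled cohort. It can, and for mathematics and wellbeing Table 3 then meets the objective. Absences and exclusions have no pooled model either, so the point survives on that reading.

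**Conclusion.** The point holds in a narrow form. One listed secondary objective has no planned analysis, pooled or separate, that includes pupils without SEND. They are about 86% of each cohort on planning figures; the achieved share may differ. The effect on precision or power for these outcomes cannot be sized from the document. The primary analysis and the sample size are untouched.

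Two stronger readings are tempting, and the documents do not support them.

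- A reader might infer that the trial promises a test of whether SEND pupils benefit more, and omits it. The statement that the Review is "anticipated to reduce absences and exclusions particularly among pupils designated SEND" is an expectation drawn from the theory of change, not an item in the list of objectives. The absence of a SEND-by-arm interaction therefore contradicts nothing stated. It remains true that setting a SEND-only result beside an all-pupil result compares overlapping samples and does not test that expectation.
- A reader might infer that the lack of a separate non-SEND model is an error for every outcome. For the marks and the SDQ, the pooled full-cohort model is a fair reading of the objective. GCSE grades are analysed in SEND pupils only, but the listed objectives do not name grades, and the marks serve the attainment aims.

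**What to change.** Preferred change: add authorised absences, unauthorised absence and exclusion for all pupils to Table 1, and for both cohorts to Table 3. Use the model types and baseline absence covariates of Table 4, with FSM added as in the other Table 3 rows. Report the estimate in non-SEND pupils alongside and label all of it secondary. While editing Table 1, reconcile its two absence rows with the text: it describes the unauthorised row as a count of authorised absences and the authorised row as a binary indicator of unauthorised absence.

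Alternative: narrow the Objectives and the Abstract so that absences and exclusions are claimed for SEND pupils only.

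Optional and exploratory: include SEND status and a SEND-by-arm interaction in the full-cohort models, and report the interaction with its 95% confidence interval. A random SEND slope in every model is more than the contradiction requires. It may be hard to fit for exclusion, with about 25 SEND pupils per school, if events are sparse.

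Cost: 3 outcomes × 2 cohorts = 6 more secondary models and their estimates. If the non-SEND estimate is obtained by refitting to non-SEND pupils rather than from an interaction term, that means up to 6 further fits. The article describes no extra data collection that this would need. The choice should be fixed before outcome data are obtained in September 2023.

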### Trial design {8}

To test these hypotheses, we will conduct a two-arm pragmatic parallel cluster randomised controlled trial with allocation at the school level (allocation ratio 1:1). This involves the recruitment of a sample of schools from across England that are subsequently assigned at random to intervention and control groups; the intervention schools receiving the intervention, the control school prohibited from doing so.

Schools are chosen as the unit or level at which randomisation occurs because of the ‘whole-school’ nature of the intervention. This feature of the intervention makes the randomisation of individual pupils or whole classes infeasible. Randomisation of schools and the measurement of outcomes at the pupil level implies a multi-level or hierarchical data structure, with pupils clustered within classes and classes with schools.

Randomisation will be stratified by region in order to facilitate regional recruitment and training, to avoid unnecessary delay, and to achieve balance in the number of schools within intervention and control arms within each region.

## Methods: participants, interventions and outcomes

### Study setting {9}

Data will be collected from mainstream secondary schools (for pupils aged 11–16 years) in England in five regions (see the ‘Eligibility criteria {10}’ below). A list of study sites will not be publicly available until the trial is completed, at which point it will be deposited in the EEF data archive in the Office for National Statistics (ONS) Secure Research Service (SRS).

### Eligibility criteria {10}

Inclusion criteria have been applied at the level of both the school and pupil. Schools with the following criteria were eligible for recruitment to the study sample, such that the school:
Is a mainstream secondary school.Must not have previously commissioned a WSS Review.Must be located in one of the following regions of England: North East, North West, South Central England and North West London, South West and West Midlands.SENDCo and other members of the school leadership team have not previously engaged with the WSS Review or similar audit.

Only one school per multi-academy trust (MAT) qualifies for inclusion in the trial. This is because MATs often set policy in relation to SEND centrally and we wish to avoid a situation where schools from the same MAT are assigned to intervention and control groups.

Within each eligible school the following pupils meet the inclusion criteria for this trial:
All pupils in years 8 and 9 on Tuesday 1st September 2020

### Who will take informed consent? {26a}

In order to participate in the trial, schools were required to sign a Memorandum of Understanding (MoU), which sets out their obligations as well as those of the developers and evaluators. The MoU is signed by the chair of school governors, the head teacher and the school SENDCo. Parents have been issued with a Parent Information Sheet outlining their child's involvement in the project, a Privacy Notice outlining how their child’s data will be managed and a Withdrawal Form [10]. Parents have been encouraged to discuss the project with their child before deciding whether or not to complete the Withdrawal Form.

### Additional consent provisions for collection and use of participant data and biological specimens {26b}

This trial does not involve collecting biological specimens.

## Interventions

### Explanation for the choice of comparators {6b}

Schools allocated to the control group will operate under ‘business as usual’; that is, they will not participate in the WSS Review process during the trial, but will be able to access it from September 2024. They may however decide to develop SEND provision by accessing alternative resources during the trial period. The Implementation Process Evaluation (IPE) running alongside the trial (see the ‘Discussion’ section) will gather data about this, so that this issue can be considered when interpreting results from the trial.

Schools in the control arm will receive a financial payment of £1500 in two instalments (July 2022, July 2023), on completion of the follow-up administration of the Strengths and Difficulties Questionnaire (SDQ; see the ‘Outcomes {12}’ section below).

